#### Study participants and eligibility criteria

Every Spanish-speaking patient over 18 years of age seeking treatment from a physician at our institution due to work-related shoulder complaints of a mechanical origin (i.e., related to movement repetitions at work) lasting more than 6 weeks will be eligible for our rehabilitation model. This preliminary time-based criterion for exclusion from the program is designed to prevent the inclusion of transient shoulder ailments that could adequately resolve with rest and NSAIDs (non-steroidal anti-inflammatory drugs).

### Detailed description

#### Shoulder multifactorial management intervention group

##### Patient status-based rehabilitation model construction

The clinical reasoning for patient investigation using the rehabilitation model is adapted from previously published data by Cools et al. [6]. These authors made a brilliant effort to generate a clinical reasoning algorithm to guide the clinician during the process of diagnosing shoulder impingement-related injuries. In the cited study, the authors clustered different orthopedic tests to differentiate between shoulder impingement, instability, SLAP and/or posterior capsule tightness. Thus, several tests were performed to diagnose or rule out the same clinical entity in an attempt to improve the diagnostic accuracy of the physical examination [6, 12].

Thus, in the present study, we aim to complement the model in two different ways. First, we will record the quantitative variables of ROM (°) and force output (N) for each of the orthopedic tests performed (see the primary outcome measures section for more details). This protocol supplementation will reinforce the posterior rehabilitation program by addressing the specific muscle force deficits observed during the complete evaluation, thus complementing the clinical diagnosis made during the evaluation itself. Thus, a functional deficits-based rehabilitation program that addresses both the clinical entity and the functional status of the shoulder will be prescribed.

The patient will complete the initial clinical and functional evaluation in the medical room and the laboratory. Afterwards, all the gathered information will be assembled to generate the patient-specific functional (i.e., related to the biomechanical laboratory examination) and clinical (i.e., related to the physician and laboratory examinations) status-based rehabilitation program. This program will be generated in conjunction with the physical therapy staff (Table 1). For each of the functional results (i.e., those related to force deficits or movement attenuation complaints) or clinical status deficits (i.e., those related to positive results on the orthopedic tests) identified during the examination, the physical therapist will identify the precise exercise and goal-based progression using a previously standardized goal-based rehabilitation algorithm adapted from previously published investigations targeting this issue [17, 18, 21] (Additional files 1, 2, 3 and 4).

### Outcome measures

#### Primary outcome

##### Pain

Pain levels during the complete clinical and functional examinations will be recorded using the previously validated visual analogue scale (VAS) [22] at the time of the functional examination in the laboratory setting. This qualitative test uses a 10-cm graded horizontal line ranging from 0 to 10 points. A 0-point score represents no pain at all, and a 10-point score is assigned to the worst pain ever felt. Immediately after each of the tests performed during the laboratory functional screening examination, the patient will be asked to use the scale to indicate the level of pain he or she experienced.

##### Range of motion measurement

The shoulder range of motion (ROM) will be measured using 3 iso-inertial unit STT-IBS (STT Systems, San Sebastian, Spain)-based technology.

The STT-IBS^©^ is a 9-degrees-of-freedom inertial measurement unit that integrates an accelerometer, a gyroscope and a magnetometer in each of its axes. The system measures the relative orientation, acceleration and position (along the X, Y, Z axes) of the STT-IBS^©^ sensors and sends this information to a computer with a Bluetooth-enabled host. The raw signals are processed online using iSens software (STT-Systems^©^, Spain), which provides the angular velocity, the acceleration and the angular position of each STT-IBS. Furthermore, after the preferred model is selected (i.e., flexion/extension, FLX/EXT shoulder model) and the sensor units are placed accordingly, the software provides the angular measurement of the selected movement in each plane.

After determining a reference position or zero position, the software measures this angular position as the projection of the vector position of each sensor in the corresponding plane determined by the reference sensor (i.e., the FLEX/EXT movement is measured as the projection of the position vector of the arm’s sensor in the sagittal plane determined by the sensor on the back).

The 3 STT-IBS units will be placed on the arm and forearm of the upper limb with straps (moving sensors) and at the patient’s inter-scapular level (reference sensor) with double-sided tape according to the specifications of the models provided by the manufacturer (STT-Systems, Spain; Fig. 2). The flexion/extension (FLX/EXT), abduction/adduction (ABD-ADD) and internal/external rotation (IR/ER) movements of the affected shoulder will be measured using the corresponding models.

**Fig. 2 Fig2:**
[figure not shown]
Range of Movement (ROM) measurement during the internal and external rotation evaluation using the inertial sensors. **a** Placement of the sensors (the reference sensor between the scapulas, and the others in the arm and forearm) and representation of the calculation of the angle as the projection in the sagittal plane. **b** Analysis software. **c** Example of ROM-Time curve

The first movement tested will be FLX/EXT. The patient will be asked to perform 3 maximal FLX movements starting from a neutral position (with the arm relaxed and aligned with the axial direction of the body). Three consecutive FLX and EXT movements starting from a neutral position will be performed. Next, the ABD movement will be measured. Similar to the previous movement, the patient will be asked to perform 3 consecutive ABD maneuvers, returning to a neutral position between repetitions.

Finally, the IR/ER task will be analyzed. The patients will be positioned with the arm parallel to the ground (90°ABD), with the forearm perpendicular to the arm and the ground and parallel to the trunk (Fig. 3). When ready, the patient will be asked to perform 3 consecutive IR and ER movements, returning to the initial neutral position after each repetition. If the patient does not return to the initial position between maneuvers, the test will be considered invalid.

**Fig. 3 Fig3:**
[figure not shown]
Example of a orthopedic test measurement using a dynamometer (Microfet 3, Hoggan Health)

Data analysis will be performed offline. The raw angular data of each pair of movements (i.e., flexion/extension movement) will be exported to an Excel file (Microsoft Office 2010, USA), and the maximum and minimum values will be obtained. The maximum values correspond to the FLX, ABD and IR movements. Conversely, the minimum values correspond to the EXT, ADD and ER. The mean of 3 repetitions for each movement will be obtained for further statistical analysis.

The shoulder range of motion (ROM) will be measured using 3 iso-inertial unit STT-IBS (STT Systems, San Sebastian, Spain)-based technology.

The STT-IBS^©^ is a 9-degrees-of-freedom inertial measurement unit that integrates an accelerometer, a gyroscope and a magnetometer in each of its axes. The system measures the relative orientation, acceleration and position (along the X, Y, Z axes) of the STT-IBS^©^ sensors and sends this information to a computer with a Bluetooth-enabled host. The raw signals are processed online using iSens software (STT-Systems^©^, Spain), which provides the angular velocity, the acceleration and the angular position of each STT-IBS. Furthermore, after the preferred model is selected (i.e., flexion/extension, FLX/EXT shoulder model) and the sensor units are placed accordingly, the software provides the angular measurement of the selected movement in each plane.

After determining a reference position or zero position, the software measures this angular position as the projection of the vector position of each sensor in the corresponding plane determined by the reference sensor (i.e., the FLEX/EXT movement is measured as the projection of the position vector of the arm’s sensor in the sagittal plane determined by the sensor on the back).

The 3 STT-IBS units will be placed on the arm and forearm of the upper limb with straps (moving sensors) and at the patient’s inter-scapular level (reference sensor) with double-sided tape according to the specifications of the models provided by the manufacturer (STT-Systems, Spain; Fig. 2). The flexion/extension (FLX/EXT), abduction/adduction (ABD-ADD) and internal/external rotation (IR/ER) movements of the affected shoulder will be measured using the corresponding models.

The first movement tested will be FLX/EXT. The patient will be asked to perform 3 maximal FLX movements starting from a neutral position (with the arm relaxed and aligned with the axial direction of the body). Three consecutive FLX and EXT movements starting from a neutral position will be performed. Next, the ABD movement will be measured. Similar to the previous movement, the patient will be asked to perform 3 consecutive ABD maneuvers, returning to a neutral position between repetitions.

Finally, the IR/ER task will be analyzed. The patients will be positioned with the arm parallel to the ground (90°ABD), with the forearm perpendicular to the arm and the ground and parallel to the trunk (Fig. 2). When ready, the patient will be asked to perform 3 consecutive IR and ER movements, returning to the initial neutral position after each repetition. If the patient does not return to the initial position between maneuvers, the test will be considered invalid.

Data analysis will be performed offline. The raw angular data of each pair of movements (i.e., flexion/extension movement) will be exported to an Excel file (Microsoft Office 2010, USA), and the maximum and minimum values will be obtained. The maximum values correspond to the FLX, ABD and IR movements. Conversely, the minimum values correspond to the EXT, ADD and ER. The mean of 3 repetitions for each movement will be obtained for further statistical analysis.

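### As written, the frontal-plane task contains no adduction movement, yet its minimum angle is scored as adduction (ADD) within the primary range-of-motion outcome

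*Protocol article*

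**What the plan says.** All of this is in the protocol article, under Outcome measures, Primary outcome, Range of motion measurement, unless another section is named.

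- **What is to be measured.** Flexion/extension is listed together with "abduction/adduction (ABD-ADD) and internal/external rotation (IR/ER) movements of the affected shoulder will be measured using the corresponding models".
- **Angle scale.** "After determining a reference position or zero position, the software measures this angular position" as a projection in the plane set by the reference sensor.
- **Sagittal task.** "Three consecutive FLX and EXT movements starting from a neutral position will be performed". Neutral is described there as the relaxed arm in line with the body axis.
- **Frontal task.** "Next, the ABD movement will be measured". The instruction is: "Similar to the previous movement, the patient will be asked to perform 3 consecutive ABD maneuvers, returning to a neutral position between repetitions".
- **Rotation task.** Internal and external rotation are both performed, with a return to the starting position each time.
- **Scoring.** Maxima are read as flexion, abduction and internal rotation. "Conversely, the minimum values correspond to the EXT, ADD and ER". Each movement is averaged over three repetitions and passed to the statistical analysis.
- **Analysis and power (Statistics and sample size).** Mean ROM changes are compared with a paired t-test at p < 0.05. At least 80% power is promised for every primary outcome variable.

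The ROM text is printed twice. Both copies give the same frontal task and the same scoring rule.

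**The concern.** A minimum angle measures a movement only if the patient makes that movement. Two of the three pairs meet this condition. In the frontal pair the written task goes from neutral into abduction and back to neutral, so the lowest point of the trace is wherever the arm came to rest. Scoring that point as ADD gives a primary variable that does not depend on how far the patient can adduct.

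If the task is run as written, a non-significant pre/post ADD result could be taken as no recovery of adduction, and a significant one as benefit. Neither reading would be justified. The power commitment would also cover a variable for which no sample size can deliver power.

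**Working it through.** **Setting the task against the score**

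| Pair | Movements requested | Maximum scored as | Minimum scored as | Is the minimum a performed movement? |
|---|---|---|---|---|
| Sagittal | flexion and extension | FLX | EXT | yes |
| Frontal | abduction, return to neutral | ABD | ADD | not as written |
| Rotation | internal and external | IR | ER | yes |

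The mismatch affects 1 of 6 directions (3 pairs × 2).

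**What the minimum contains under the written task**

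The plan gives no figure for adduction, so there is none to reproduce. The values below are assumptions for illustration, except that the abduction change equals the 25° cited in Statistics and sample size.

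Inputs: mean peak abduction 90° before and 115° after; error e in returning to neutral, with mean 0 and SD σ of 0°, 2° or 5°; zero reference at neutral (offset 0°) or 10° away from it.

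The trace starts at neutral and ends at neutral plus e, so its minimum is approximately

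offset + min(0, e), with expected value offset − σ/√(2π).

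- σ = 0: offset − 0
- σ = 2: offset − 2/2.507 = offset − 0.80
- σ = 5: offset − 5/2.507 = offset − 1.99

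A simulation of the three-repetition average (4,000 patients per visit) agrees:

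| σ | Offset | ADD before | ADD after | ADD change | ABD change |
|---|---|---|---|---|---|
| 0° | 0° | 0.0° | 0.0° | 0.0° | 24.8° |
| 2° | 0° | −0.8° | −0.8° | 0.0° | 25.0° |
| 5° | 0° | −2.0° | −2.0° | 0.0° | 24.6° |
| 0° | 10° | 10.0° | 10.0° | 0.0° | 24.7° |
| 2° | 10° | 9.2° | 9.2° | 0.0° | 25.1° |
| 5° | 10° | 8.0° | 8.0° | 0.0° | 24.8° |

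True adduction range appears nowhere in the formula. If no adduction is performed and return error is alike at both visits, the expected ADD change is 0 whatever the true change. The rejection rate of the test is then its 5% significance level at any sample size.

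The score can still move. If σ fell from 5° to 2° between visits, mean ADD would shift by −0.80 − (−1.99) = 1.2° with no change in adduction range. Such a shift would reflect positioning, not the outcome named.

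**Contrast if adduction is performed**

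With an assumed movement past neutral of 20° before and 30° after, the same scoring rule gives −20° and −30°, and the 10° change is visible. The scoring rule is therefore sound in itself; it needs a task that matches it.

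**The case against.** The strongest reply is that a paired task was intended and one sentence was written too briefly. Three pieces of text support this. The section says the abduction/adduction pair will be measured with its own sensor model. The data handling is described in terms of pairs of movements. The frontal instruction opens by likening the task to the preceding one, in which both directions are performed. The ROM block is also loosely edited, being printed twice with differing figure references. All of this stands, and it means the article does not show that adduction goes unperformed in the laboratory. It does not remove the mismatch, because both copies go on to specify abduction only. Nor is this a detail left to a fuller document: the article states both the task and the rule, and they do not fit.

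It could also be said that returning from abduction is itself adduction. That is true of the direction of motion, but the score is the lowest angle, which on return is the neutral end point.

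A reader might infer more than the text supports:

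- *ADD is zero by construction.* The article does not equate the zero reference with neutral. With another zero the score is an offset.
- *ADD cannot change.* Overshoot, drift or incomplete return can move it, although none of these measures adduction range.
- *Power is 5%.* This holds only if adduction is not performed and return error is stable between visits.
- *The sample size or the main comparison is undermined.* The sample-size argument uses abduction, which is scored from the maximum. The historical controls have no functional evaluation, so ROM does not enter the between-group comparison. Adduction range is not named in the prescription table or in the cost analysis.

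**Conclusion.** The task description and the scoring rule contradict each other for one of the six ROM directions in the primary outcome. Followed as written, ADD reflects the neutral position plus return and sensor error. It holds no information on adduction range, its pre/post test is uninterpretable, and the 80% power commitment cannot apply to it.

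This rests on two readings: that no adduction past neutral is performed, and that neutral in the frontal task is the relaxed-arm position defined for the sagittal task. If adduction past neutral is in fact performed at each visit, the measurement is sound and only the task text is wrong. In either case the other five directions stand, including abduction. The point is worth correcting because the variable is classed as primary, but it does not threaten the study as a whole.

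**What to change.** State in the frontal-plane task whether the patient moves past neutral into adduction, and bring the scoring rule into line, in both printed copies of the text.

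- **If adduction is performed:** describe it in the instruction as is done for flexion/extension and internal/external rotation, with the same task at every visit. Keep ADD as the minimum.
- **If it is not performed:** remove ADD from the minimum-value list and from the primary ROM variables, leaving five directions, or add the movement to the recording.

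In either case, say whether the zero reference is the neutral position. The cost is a text edit, or a few seconds per visit if the movement is added. Sample size and the abduction measure need no change.

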##### Isometric peak force evaluation

Throughout the screening examination, each of the orthopedic tests will be performed using a hand-held dynamometer (MicroFeet 1 Hoogan Industries, USA) to register the peak force (N) exerted during each task in addition to the standard clinical interpretation of the pain elicited during the maneuver. Three repetitions will be performed for each limb at each testing position. The first repetition will serve as familiarization, whereas the subsequent two repetitions will be recorded for further analysis.

#### Secondary outcome measures

##### Measures of self-reported shoulder function

Self-reported shoulder function will be registered using the Simple Shoulder Test Questionnaire (SST). The questionnaire consists of 12 items answered with dichotomous responses (yes/no). Two questions are related to pain, 7 are related to function and strength, and 3 are related to range of motion perceptions. The minimum clinically important difference between pre- and post-rehabilitation evaluations was set at 2 to 2.33 points [23]. The questionnaires will be completed each time the patient undergoes a functional evaluation at the laboratory.

##### Cost effectiveness analysis

When the study concludes, the number of rehabilitation and medical visits administered and the number of working days lost among the participants will be analyzed. Thus, the economic burden of the rehabilitative process (including both medical costs and the costs of missed work) will be determined for comparison with historical cohorts from the same medical institution (60 patients recruited the year before the OCBRA model is implemented). The number of overall rehabilitation and medical visits made will by multiplied by their typical economic costs at the hosting medical institution. The number of sessions administered and the number of work days missed will be provided by the mutual insurance society for work-related injury management. The economic burden of both medical costs and missed work days will be provided by the same institution following the recommendations of the National Social Health Agency of the Spanish Heath Service Ministry. The cost effectiveness ratio will be calculated as the number of visits + missed work days divided by the sum of the economic burdens.

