**Fig. 1 Fig1:**
[figure not shown]
Multi-etiologic shoulder injury management model for rehabilitation algorithm description

Full recovery will be determined by negative results on the last medical examination (for both the patients in the OCBR group and the clinical cohorts serving as controls) and positive results on the biomechanical evaluation (only for the patients in the OCBR algorithm). As the clinical cohorts will not undergo functional evaluations, the time to full recovery and the number of physician and physiotherapy visits will be analyzed to compared the cost-effectiveness of the two injury management models (the proposed vs. previous typical care).

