### Trial status

The trial will start recruitment on January 2017. The trial will remain undecidedly open given that the present intervention program is the standard for shoulder injury care at the friendly society for work-related injuries management wherein the study is being performed. Once 100 patients are enrolled, a case- series retrospective study will be performed to compare the cost efficiency in terms of time duration, number of physical therapy and physician visits perceived and economical burden of the present shoulder injury management program vs. historical cohorts of patients receiving care at our institution.

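### The cost-effectiveness ratio divides resource use by the cost of that same use, so it has no effect term and no direction of benefit

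*Protocol article*

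**What the plan says.** Under Secondary outcome measures, the subsection Cost effectiveness analysis gives the rule: "The cost effectiveness ratio will be calculated as the number of visits + missed work days divided by the sum of the economic burdens".

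The same subsection describes the denominator. In general terms, "the economic burden of the rehabilitative process (including both medical costs and the costs of missed work) will be determined". For visits it gives the method: "The number of overall rehabilitation and medical visits made will by multiplied by their typical economic costs at the hosting medical institution". For missed work it gives only the source: "The economic burden of both medical costs and missed work days will be provided by the same institution". No unit price is stated for either.

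Two other places describe the economic comparison without the ratio. The paragraph on full recovery after Fig. 1 says that, because the historical cohort has no functional evaluation, "the time to full recovery and the number of physician and physiotherapy visits will be analyzed" in order to compare the two models. Trial status says a study will "compare the cost efficiency in terms of time duration, number of physical therapy and physician visits perceived and economical burden" against historical patients. The analysis text in Statistics and sample size does not mention the ratio.

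**The concern.** A cost-effectiveness measure sets a difference in cost against a difference in health effect. This ratio has neither. Its numerator adds visits to missed work days, which are different units and are both things the programme hopes to reduce. Its denominator is the price of those same visits and days. Pain, range of motion, force, self-reported function and recovery do not enter, and nothing is differenced between the two models.

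The Discussion hopes for faster return to activity and a smaller economic burden. The only cost-effectiveness ratio that the article defines may not register such a gain, and it may make one kind of saving look like a gain and another look like a loss. A reader given the ratio for each group could not say which value is better.

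**Working it through.** **Inputs.** The form of the ratio and the visit costing come from Cost effectiveness analysis. Counts are to come from the insurer ("The number of sessions administered and the number of work days missed will be provided by the mutual insurance society"). The article gives no prices and no expected counts, so every number below is an assumption for illustration. A constant cost per missed day is also an assumption; the article states multiplication by a typical cost for visits only. There is no published value of the ratio to reproduce.

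**Formula.** Let V = visits, D = missed days, and pV, pD = their unit costs. Then

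R = (V + D) / (pV·V + pD·D).

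The inverse, 1/R, is the average price of one visit-or-day.

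**Step 1: scaling.** Multiply V and D by any k. Then k(V + D) / [k(pV·V + pD·D)] = R. Halving all resource use leaves R unchanged, whatever the prices.

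**Step 2: direction.** With C = pV·V + pD·D,

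- dR/dD = V(pV − pD)/C²
- dR/dV = D(pD − pV)/C²

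These always have opposite signs. If a day costs more than a visit, R rises when only days fall and falls when only visits fall. If a visit costs more, both directions swap. If the prices are equal, R is a constant.

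**Step 3: numbers.** Assumed visit price 30; R per 1000 units of cost.

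| Visits, days | Day price 60 | Day price 100 | Day price 200 |
|---|---|---|---|
| 30, 60 (base) | 90/4500 = 20.00 | 90/6900 = 13.04 | 90/12900 = 6.98 |
| 15, 30 (both halved) | 45/2250 = 20.00 | 45/3450 = 13.04 | 45/6450 = 6.98 |
| 30, 30 (days halved) | 60/2700 = 22.22 | 60/3900 = 15.38 | 60/6900 = 8.70 |
| 15, 60 (visits halved) | 75/4050 = 18.52 | 75/6450 = 11.63 | 75/12450 = 6.02 |

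The swap, with visit price 100 and day price 30: base 90/4800 = 18.75; days halved 60/3900 = 15.38; visits halved 75/3300 = 22.73.

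**Step 4: separating rehabilitation from medical visits.** Assume 30 rehabilitation visits, 5 medical visits and 60 days, with prices (rehabilitation / medical / day) of 20/50/80, 30/60/100, 50/50/50 and 15/100/200.

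- All counts halved: R is unchanged in all four sets (for 30/60/100, 95/7200 = 47.5/3600 = 0.013194).
- Only days halved: R rises 17% to 27% in the three unequal-price sets and not at all at equal prices.
- Only rehabilitation visits halved: R falls 10% to 14% in the same three sets and not at all at equal prices.

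**Step 5: relaxing the conditions.**

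- Days and total visits halved, but with the visit mix shifted (10 rehabilitation, 7.5 medical, 30 days): new/base = 0.94 to 1.00. For 30/60/100, 47.5/3750 = 0.012667, and 0.012667/0.013194 = 0.96.
- All use halved, with an assumed fixed cost of 200 per patient added on the OCBRA side only: new/base = 0.92 to 0.97. For 30/60/100, 47.5/3800 = 0.0125, and 0.0125/0.013194 = 0.947.

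In both cases R can move, but it reflects the price mix or the added cost, not a benefit.

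**The case against.** The strongest reply is about reach. The ratio is the last sentence of a secondary-outcome subsection. The primary outcomes are pain, range of motion and force, and the statistics section never uses the ratio. Interpretable economic comparisons are planned beside it: visits, missed days and total burden in Cost effectiveness analysis, time to recovery and visits in the paragraph after Fig. 1, and duration, visits and burden as separate terms in Trial status. In the illustration, a halving of use would appear plainly as 6900 against 3450 in the total-burden comparison. All of this stands.

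It also stands that exact invariance is conditional. It needs a constant cost per missed day, which the article does not state, and an unchanged mix of visit types. The rises and falls depend on whether a day or a visit is dearer.

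A further reply is that missed work days are themselves an outcome, so the numerator does hold an effect. This does not stand. They are added to visits, fewer of them is better, and they are priced again in the denominator. Inverting the ratio does not help either, since that gives an average unit price.

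Finally, replacing the ratio with an incremental cost-effectiveness ratio (ICER) as the default would bring problems of its own. If OCBRA is both cheaper and faster, an ICER is hard to interpret. Patients who do not progress are referred back to the physician for other treatment, so some may never have a recovery date and a simple mean of days to recovery is undefined for them. Full recovery also requires a biomechanical criterion in the OCBRA group only. These points stand and shape the fix.

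**Conclusion.** The formula is wrong as written and should be fixed. With constant unit costs (stated for visits, assumed for missed days), it is the reciprocal of an average unit price. It is unchanged when every type of visit and missed days are halved together. Where days and visits are priced differently, it moves in opposite directions for the two kinds of saving. The illustrative sizes rest on assumed prices and counts; the invariance and the opposite signs are algebra and do not.

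A reader might infer that the comparison with the historical cohort as a whole cannot show OCBRA to be cheaper, or that the ratio is the trial's headline result. The article supports neither. The defect is confined to one derived secondary index, and the separate comparisons of visits, missed days, time to recovery and total burden are not touched by it. Because that index is the one labelled cost-effectiveness, no cost-effectiveness conclusion should be drawn from it.

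**What to change.** Delete the ratio. As the cost-effectiveness result, report side by side:

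1. the OCBRA-minus-historical difference in mean total cost per patient, with a bootstrap 95% CI;
2. the difference in time to full recovery, using the one definition available in both groups (a negative final medical examination), with patients who have not recovered treated as censored.

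Report an ICER only if one model is both costlier and more effective, with cost and effect bootstrapped jointly. If missed work days are already costed in item 1, do not also use them as the effect.

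The cost is one paragraph of wording and a little more analysis, on data already planned for collection. Primary outcomes, sample size and data collection do not change.
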